### Sample size

At the time we were developing the study we could find no systematic reviews of lifestyle interventions in pregnant women, so we based our sample size on a systematic review of interventions with obese adults, which found a mean weight loss of 7.9 kg (8.5%) during the first 6 months of interventions involving diet and exercise, after which weight was gradually regained, by 48 months a mean weight loss of 3.9 kg (4%) was maintained [28]. Results for trials which included only obese women (mean BMI+/=30 at baseline) demonstrated weight loss of a similar magnitude at 12 months [28]. In order for an individually randomised trial to have 80% power to detect a moderate effect size of 0.333 for a difference in BMI at 12 month follow-up of 1.5 kg/m^2^ (SD = 4.5), at a 5% significance level, 143 women per group would be required. Little pertinent data are available for the estimation of the intra-cluster correlation coefficient (ICC). Assuming an ICC of 0.02, if 20 maternity units were recruited across England and Wales, a variance inflation factor of 1.4 would result, so the total sample size is therefore inflated to 400 to detect the difference stated above and we would require an average of 20 women per unit. This would allow for a variance inflation factor of 1.4 (ICC = 0.02) [73]. In trials investigating weight management interventions in pregnant women, losses to follow-up range considerably from 5% to 38% [58,59,74-76], therefore we have allowed for a drop out of 30% and intend to recruit 570 women.

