### Analysis

#### Quantitative analysis

The main analysis will be by intention to treat and will compare the primary outcome of BMI at 12 months postpartum in the intervention and control groups. Multilevel modelling will be used to account for clustering within antenatal unit and individual effects. A two level linear regression model will include baseline BMI (measured at recruitment) as a covariate. Both levels will be considered ‘random effects’ i.e. patients and units are drawn randomly from a larger population of patients and units. Cluster level variables include those used to balance the randomisation: antenatal unit size; proportion of women with BMI +/=30, geographic location and ethnic mix.

For the BMI data, positively skew distributed form is anticipated and will be checked prior to analysis. Log transformation will be considered, not only to deal with the non-normality but to allow interpretation of differences between arms in percentage terms. To further aid clinical interpretation of the intervention effect, analysis of log transformed weight at 12 months postpartum will also be considered, with baseline log weight and log height as covariates. The results can then be expressed in terms of BMI or weight along with a 95% confidence interval. The intra-cluster correlation (ICC) for the primary outcome will be calculated and reported.

Intention to treat analysis will be used for all secondary outcomes. Analysis of secondary outcomes will also use multilevel modelling incorporating baseline scores as covariates where appropriate. Two level linear regression models will be used for outcomes such as pregnancy weight gain and waist-to hip ratio and validated questionnaire scores, while logistic models will be used for clinical event outcomes. 95% confidence intervals for the intervention effect will be calculated. The ICC for each secondary outcome will be calculated and reported.

The impact of individual demographic factors as well as theoretical mediators (self-efficacy, social support, intrinsic motivation and self-regulation) on the intervention effect using interaction terms included in the main analysis models will be examined. Individual demographic variables include age, ethnicity, smoking status, previous weight loss history, psychological wellbeing and social class. We also intend to carry out tests for mediator variables [97].

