As well as examining number of sessions attended, patterns of missed sessions and compliance with the intervention will also be explored. A complier average causal effect (CACE) analysis will be carried out for the primary outcome to assess the effect of the intervention in those who complied [97,98]. An investigation of required minimum dose of intervention will be carried out. A per- protocol analysis will include only those participants in each arm that received treatment as randomised excluding those in the control arm attending weight loss groups.

No formal subgroup analyses are planned. However, exploratory analyses of the impact of social class, parity, ethnicity (if numbers permit), smoking status and initial BMI on the effect of the intervention will be carried out. This will be achieved by fitting a subgroup by randomised group interaction term to the multilevel model.

If the proportion of missing primary data is substantial (more than 10%) a series of sensitivity analyses will be carried out to determine the likely effects of missing data [99-101]. The intention is to use multiple imputation to generate complete datasets for analysis. Imputation models will include those variables in the analytic model plus any additional variables associated with missingness and outcome. Self-reported weight (from the minimum dataset) and Slimming World session weight data may be used to replace missing weights where appropriate in secondary analyses. Further sensitivity analyses may be carried out to examine the effects of removing women who are known to be pregnant at the 12 month postpartum follow-up, as well as those who have recently given birth to a second baby. The assumptions of all models used for primary and secondary analysis will be checked.

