Short and long term effects of the intervention can be examined using repeated measures analysis of intermediate weight measurements. The difference in weight at 6 months postpartum will also be examined. The proportion of participants who lost 5% of their weight (weight at 6 months postpartum compared to baseline) will be calculated for each arm. The difference between groups will be examined to identify if they maintained that loss. The association between subsets of clinical outcomes will also be investigated and a total count of all clinical outcome events will be calculated and compared between trial arms. Individuals lost to follow-up will be compared to those who complete follow-up to identify potential sample bias.

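### The main analysis uses only 12-month BMI although 30% loss is planned for; the measured weights at 36 weeks, 6 weeks and 6 months should support the primary estimate

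*Protocol article*

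**What the plan says.** All places are in the protocol article.

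- **Main analysis** (Quantitative analysis). It is described as intention to treat and compares BMI at 12 months postpartum between arms. "A two level linear regression model will include baseline BMI (measured at recruitment) as a covariate". The two levels are women and maternity units, not occasions within women.
- **Missing data** (same section). "If the proportion of missing primary data is substantial (more than 10%) a series of sensitivity analyses will be carried out". Multiple imputation follows directly as the intended method. The imputation model takes the analysis-model variables plus unnamed further variables related to missingness and outcome. Self-reported and group-session weights may replace missing values, but only in secondary analyses.
- **Intermediate weights** (same section). "Short and long term effects of the intervention can be examined using repeated measures analysis of intermediate weight measurements". The 6-month difference and the proportion losing 5% of weight are also listed. None of these feeds the main analysis.
- **Expected loss** (Sample size). Earlier trials' "losses to follow-up range considerably from 5% to 38"%, and "therefore we have allowed for a drop out of 30% and intend to recruit 570 women".
- **Weight schedule** (Table 1). Calibrated scales at baseline, 36 weeks' gestation, and 6 weeks, 6 months and 12 months postpartum, with no distinction by arm.

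**The concern.** The protocol calls more than 10% missing primary data substantial and plans for three times that. Even so, the result that leads the report comes from a model that leaves out every woman without a 12-month BMI. The article never uses the term complete case, but a single-time-point, two-level model amounts to one.

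In a weight-management trial, a woman's weight course after delivery may affect whether she attends the last visit. That influence may differ by arm: treatment is open, one arm has been in a weekly weighing group, and the section Protecting against bias accepts that outcome collectors will be hard to blind and takes steps against differential dropout. If heavier women are lost more readily from the intervention arm than from the control arm, the remaining intervention women look lighter than they should and the lead estimate flatters the programme. If the difference between arms runs the other way, so does the bias. The scheduled intermediate weights carry information on exactly this, and they are kept out of the lead estimate.

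**Working it through.** **1. The plan's own figures.** The target is 1.5 kg/m2 with SD 4.5, for "80% power to detect a moderate effect size of 0.333".

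- Per arm, two-sided 5%: 142 by the normal formula and 143 by the noncentral t. The stated figure is 143.
- Clustering: 286 × [1 + (20 − 1) × 0.02] = 286 × 1.38 = 395; with the stated factor, 286 × 1.40 = 400. The stated figure is 400.
- Dropout: 400 / 0.70 = 572. The stated figure is 570.
- At the planned loss: 570 × 0.30 = 171 women without the primary outcome and 570 × 0.70 = 399 analysed. Power is 80.3% (factor 1.40) to 80.9% (factor 1.38).

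The sample size reproduces and already covers the loss. The point is about bias and, to a lesser degree, precision.

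**2. Delta shift.** Suppose missing intervention women are heavier than the model assumes by d, with no such departure in controls. Then bias = missing share × d.

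| Missing share | d = 1 | d = 1.5 | d = 2 |
|---|---|---|---|
| 10% | 0.10 | 0.15 | 0.20 |
| 30% | 0.30 | 0.45 | 0.60 |
| 38% | 0.38 | 0.57 | 0.76 |

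(kg/m2; at 30% loss this is 20%, 30% and 40% of 1.5.)

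**3. Simulation with no true effect.** None of these inputs is in the protocol except the 30%; they are assumptions. BMI change from baseline has SD 2.5 at 6 months and 2.7 at 12 months, the slope of 12-month on 6-month change is 0.8, and loss is about 30% in each arm. The odds of loss rise by 1.15 or 1.3 per kg/m2 of 6-month change.

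| Scenario | OR 1.15 | OR 1.3 |
|---|---|---|
| Dependence in intervention arm only, complete case | −0.20 | −0.36 to −0.37 |
| Same dependence in both arms, complete case | +0.003 | −0.008 |
| Intervention arm only, 6-month weight used, all dropouts have it | below 0.01 | below 0.01 |
| Same, 50% of dropouts lack the 6-month weight | −0.09 | −0.15 |
| Same, 75% of dropouts lack it | −0.14 | −0.25 |

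As shares of the target: 0.20 / 1.5 = 13% and 0.37 / 1.5 = 25% for complete case; 0.09 / 1.5 = 6% and 0.25 / 1.5 = 17% for what remains.

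The two calculations agree. Dividing the complete-case bias by the missing share gives 0.20 / 0.30 = 0.67 and 0.37 / 0.30 = 1.23 kg/m2. The odds ratios of 1.15 and 1.3 therefore mean that lost intervention women are on average about 0.7 to 1.2 kg/m2 heavier than those retained.

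**4. Second simulation.** It used 20 units of 28 women, ICC 0.02, a baseline to 12-month correlation of 0.8, a 6-month weight in every woman, and a steeper dependence (log-odds 0.5 to 1 per SD) in the intervention arm only. Complete case gave −0.26 to −0.60 with no true effect; using the 6-month weight gave 0.02 or less. With random loss or equal dependence in both arms, neither method showed material bias, and using the 6-month weight cut the empirical standard error by about 3% to 7% (for example 0.387 to 0.375, and 0.391 to 0.365).

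**The case against.** **The remedy is partly in the plan already.** If 6-month BMI predicts both loss and 12-month BMI, it qualifies as an auxiliary variable under the protocol's imputation rule, so measured weights can enter a planned analysis of the primary outcome. An observed-data primary model with imputation as sensitivity is also conventional. This stands as far as it goes: the intermediate weights are not shut out of all work on the primary outcome. But they are not named, and the analysis that may use them does not lead.

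**Imputation might be meant as primary.** The sentence on producing completed datasets does not say which result leads. It follows the sensitivity-analysis sentence, which argues against that reading. If it was meant, the lead analysis is ambiguous and needs stating. Nor is this detail left to an analysis plan, because the article itself ranks the analyses.

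**The bias rests on an asymmetry for which the protocol has no data.** This stands. A reader might infer that the main model is valid only if dropout depends on nothing beyond arm and baseline BMI. That is too strong: dropout may depend on anything unrelated to 12-month BMI given the covariates, and the contrast also survives weight-related dropout of similar strength in both arms.

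**The remedy is imperfect.** A reader might infer that the 6-month weight removes the bias. It does so only if the women lost at 12 months were weighed at 6 months, and the protocol does not say how many will be.

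**The size is modest.** The planned standard error is about 4.5 × √(2/143) = 0.53, before any gain from baseline adjustment. The bias of 0.20 to 0.37 is below that, and 30% is an allowance rather than a forecast. All true, but the bias is systematic and avoidable in part with data already scheduled.

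**Conclusion.** The point holds as a weakness in how the analyses are ranked, not as an error or contradiction. At the planned loss the lead estimate omits about 171 of 570 women and ignores three scheduled post-baseline weights. It is biased if dropout depends on later weight differently by arm. If so, and only in the intervention arm at the assumed odds ratios, the bias is about −0.20 to −0.37 kg/m2, or 13% to 25% of the target. Using the 6-month weight would remove between about a third of this and all of it, depending on how many dropouts have that weight.

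The documents do not show that such bias will occur or that it would favour the intervention; both depend on the assumed pattern of loss. The case for change is that the alternative needs a weaker missing-data assumption, gains a little precision even when there is no bias, and needs no new data.

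**What to change.** State which result leads, and make it one of these:

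- the 12-month arm contrast from a multilevel repeated-measures model of BMI at 36 weeks, 6 weeks, 6 months and 12 months (occasions in women in units), with arm by visit, baseline BMI by visit, a unit random effect and an unstructured covariance within women; or
- the existing two-level model after multilevel multiple imputation carried out by arm, naming the 36-week, 6-week and 6-month weights in the imputation model.

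Keep the complete-case two-level model as a sensitivity analysis. Add a delta-adjusted analysis in which departures can differ by arm, and report how many women lost at 12 months had a 6-month weight.

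The cost is a change of wording and slightly more modelling work. Visits, data collection and the required sample size do not change. Neither option protects against dropout that depends on later weight that was never observed, which is why the delta-adjusted analysis is needed.

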### Design

The study is a cluster randomised controlled trial; the maternity units, rather than individual participants, are the units of randomisation. This is to minimise risk of contamination of control participants through two potential mechanisms. Firstly, the use of aspects of the intervention with control participants by site midwives who have been trained in study procedures and secondly, the passage of information regarding the intervention between intervention and control participants who are acquainted and attend the same maternity unit.

In addition to receiving usual NHS care, all study participants will be provided with 2 study leaflets: 1) a Food Standards Association eating during pregnancy leaflet detailing foods which should be avoided during pregnancy and 2) an exercise during pregnancy leaflet detailing recommended physical activity during pregnancy and warning signs for when to stop exercise and seek medical attention. Participants attending intervention sites will also receive the HELP Study intervention which is described below. Participants attending control sites will only receive usual care and the leaflets.

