### Study intervention

A logic model (shown in Figure 1) describing the theory of the intervention was developed. This illustrates the key inputs, outputs/behaviours and outcomes of the intervention. Participants attending intervention sites will have the opportunity to attend free, weekly, 1.5 hour weight management group sessions from the point of recruitment (between 12 and 20 weeks gestation) up until 6 weeks postpartum. At this time point they will receive one voucher for a free Slimming World session at a ‘normal’ community group. They will also receive two intervention phone calls from the Intervention Midwife at 3 and 6 months postpartum in order to provide longer term support and encouragement. Long term intervention contact helps sustain weight loss [61] and telephone support can be effective in weight loss interventions [62]. Assuming normal gestation of between 37 and 42 weeks and depending on when women were recruited, the intervention period will be up to 56 weeks in total.

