**Figure 1 F1:**
[figure not shown]
HELP Intervention Logic Model mapping the theory of the intervention.

The intervention sessions will be held in NHS Antenatal Clinics and will be run jointly by an NHS midwife and a Slimming World consultant. There are four main components of the intervention group sessions: 1) healthy eating, 2) physical activity, 3) midwifery advice and 4) behavioural component.

1) The healthy eating component

Slimming World, a major UK based commercial slimming organisation has developed a flexible weight management and healthy eating programme called “Extra Easy”, which follows current UK government recommendations for a healthy diet including the “Eat Well Plate”. The diet consists of a combination of different food types: approximately 80% combined from fruit, vegetables, carbohydrates and protein; a smaller section for milk and dairy; and an allowance for foods high in fat or sugar. Other than limiting the intake of high fat or high sugar foods, it is not a ‘restrictive’ diet. Pregnant women are offered advice to encourage them to eat additional healthy extras to ensure they have adequate calcium and fibre intake. The programme utilises a “food optimising system” to encourage adherence to the healthy eating plan by considering and modifying energy density and satiety, complemented by flexibility of food options.

2) The physical activity component

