In order to prevent over-exertion, women will be advised to only partake in moderate physical activity and they will be asked to utilise the Borg Scale of Perceived Exertion [66] each time they do any physical activity to monitor levels of exertion. The Borg scale runs from 6 (no exertion) to 20 (maximum exertion), women will be asked to engage in activity that is ‘somewhat hard’ (around 12-14 on the scale). Information regarding warning signs to terminate exercise and when medical advice should be sought will be provided. However, for the majority of women, exercise is safe for both mother and foetus throughout pregnancy and initiating moderate exercise or continuing exercise is recommended in most pregnancies [63].

3) The Midwife component

In addition to the usual NHS midwifery care, the Intervention Midwife will be available to provide advice regarding pregnancy and lifestyle, as well as provide additional support in topics that women may be anxious about like labour choices and breast feeding. Evidence indicates that obese women are less likely than their non-obese counterparts to breast feed [67] and breast feeding is associated with reduced postpartum weight retention [68]. The study is recommending a healthy, balanced and unrestricted diet in pregnancy and therefore foetal weight should not be impaired. Any woman in the intervention group who loses a cumulative 3 kg over the pregnancy will be reviewed by the Intervention Midwife and asked to complete a 7-day food diary to confirm that she is eating a healthy amount of food. If necessary, the Intervention Midwife will refer the participant to their obstetrician. Participant safety will be the responsibility of the Intervention Midwife and any concerns will be referred to an appropriate medical practitioner as per normal protocol within the health care service.

Each session will include the following:

4) Behavioural component

•The weighing session where each woman attending will be weighed.

•New members will be welcomed and achievements of the group reviewed.

•Nutritional advice will be given and the group will discuss topics such as foods to avoid in pregnancy, sharing ideas, recipes, eating out ideas. The women will also be given access to Slimming World resources such as recipe books and magazines.

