### Follow-up & drop out

Baseline data will be collected by local PIs. Follow-up data will be collected by local PIs or research staff in each centre, or network research staff. For units in Wales this will be the Clinical Studies Officers employed by National Institute for Social Care and Health Research Clinical Research Collaboration (NISCHR CRC), in England the research nurses employed by the Comprehensive Local Research Networks (CLRN). The follow-up visits will be completed in the participants’ home or at a location of the participants’ choice. The follow-up appointments are timed to occur at important milestones both pre and postnatally: 36 weeks gestation, 6 weeks postpartum, 6 months postpartum and 12 months postpartum.

Every effort will be made to reduce loss to follow-up: women will be visited at a convenient location of their choice for all follow-up appointments. In order to improve response rates, participants will be contacted to rearrange any missed follow-up appointments, participant-nominated contacts will be collected at baseline in order to facilitate contact at follow-up appointments, participants will be posted study updates in the form of newsletters and follow-up calendars, and each participant will be provided with a £10 high street voucher as a thank you for completing each follow-up. A HELP study website will be used to provide study updates (http://medicine.cf.ac.uk/help-study/), and a minimum dataset will be developed to collect follow-up data by telephone for those participants who are unwilling or unable to meet with the researcher.

In order to prevent resentful demoralisation in the control group, each of these women will be offered 12 weeks normal community-based Slimming World sessions free of charge after her 12 month follow-up is complete. Any woman who undergoes a miscarriage, stillbirth, neonatal death or termination of pregnancy will be given an open option whether or not they wish to continue participation in the study.

All site study staff including the Intervention Midwife and Slimming World consultant will be visited by the research team and updated via regular contact and newsletters in order to encourage continued enthusiasm. In addition, to prevent disappointment following randomisation in the control sites, if results from the study prove positive units allocated to the control group will then be offered training for their midwives in the intervention.

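### In secondary analyses, Slimming World session weights may replace missing weights, but the article describes such weights only for intervention-arm attenders and only up to 6 weeks postpartum

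*Protocol article*

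**What the plan says.** The missing-data paragraph under Quantitative analysis plans sensitivity analyses if more than 10% of primary data are missing, with multiple imputation as the intended method. It then names two substitute sources. One is self-reported weight from the minimum dataset. The other is that "Slimming World session weight data may be used to replace missing weights where appropriate in secondary analyses". No arm, visit or time window is attached.

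Other sections show where session weights come from:

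- Study intervention: women at intervention sites may attend "weekly, 1.5 hour weight management group sessions from the point of recruitment (between 12 and 20 weeks gestation) up until 6 weeks postpartum".
- Same section, session content: "The weighing session where each woman attending will be weighed". The sessions "will be run jointly by an NHS midwife and a Slimming World consultant".
- Same section, after 6 weeks postpartum: "they will receive one voucher for a free Slimming World session" at a community group. No collection of a weight from it is described.
- Design: "Participants attending control sites will only receive usual care and the leaflets".
- Follow-up & drop out, on control women: "each of these women will be offered 12 weeks normal community-based Slimming World sessions free of charge after her 12 month follow-up is complete".

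Table 1 schedules maternal weight at baseline, 36 weeks gestation, and 6 weeks, 6 months and 12 months postpartum, without distinction by arm. The telephone minimum dataset is likewise described for participants generally. Protecting against bias, in the Discussion, states that staff who deliver the intervention will not collect follow-up data.

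**The concern.** A substitute for a missing outcome should be available on the same terms in both arms. Here one of the two named sources can be filled, as far as the article describes, only for intervention women. Within that arm it exists only for women who came to the groups, and attendance is a post-randomisation behaviour plausibly related to weight. After such replacement the two arms would be missing different kinds of women.

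Timing adds a second problem. The groups stop at 6 weeks postpartum, while two of the four follow-up weights, including the primary one, fall much later. A session weight used there is a last value carried forward in one arm, over months in which weight can change. For a woman who stopped attending early, it may even be a weight from pregnancy.

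Third, in a trial whose outcome assessors will be hard to blind, the separation of delivery from measurement is one of the stated protections. Weights taken at sessions fall outside it.

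What is at stake is the supporting evidence: sensitivity analyses for missing 12-month BMI, and the secondary weight analyses (pregnancy weight gain, weight at 6 months, 5% weight loss, repeated measures).

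**Working it through.** **1. How much missing data the plan expects.** The only figures bearing on this are in Sample size, and they reproduce.

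- Two means, difference 1.5, SD 4.5, two-sided 5% (two-sided assumed), 80% power: 142 per group by the normal approximation; 142.2 to 142.5 by the t test, rounded up to 143 as stated.
- Design effect: 1 + (20 − 1) × 0.02 = 1.38, stated as 1.4. Then 286 × 1.4 = 400.4, stated as 400.
- 30% drop-out: 400 / 0.70 = 571.4, against 570 stated.

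With equal arms of 570 / 2 = 285 and equal loss (assumed), 0.30 × 285 = 85.5, so about 86 women per arm would lack a 12-month weight.

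**2. Which gaps each source could fill, as described.**

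| Source | Intervention arm | Control arm | Latest time |
|---|---|---|---|
| Telephone self-report | yes | yes | any follow-up |
| Session weight | attenders only | none described | 6 weeks postpartum |

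Two possible exceptions do not alter the second row. The community voucher and any outside groups that control women join could involve weighing, but the article describes no collection of those weights. It mentions the outside groups only when defining the per-protocol set, "excluding those in the control arm attending weight loss groups".

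**3. Age of the last possible session weight.** Taking 6 months as 26 weeks and 12 months as 52 weeks:

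- 6-month visit: 26 − 6 = 20 weeks old, at least.
- 12-month visit: 52 − 6 = 46 weeks old, at least.
- The 36-week and 6-week visits: a session weight can be close in time.

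**4. Illustration of size.** Let m be the share of the intervention arm with a missing weight, f the share of those replaced by a session weight, and b the average difference between the substituted and true BMI. The replaced women form w = mf / ((1 − m) + mf) of those analysed, and the intervention mean shifts by w × b. Only the 30% for m and the 10% trigger come from the article; f and b are assumptions.

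| m | f | b (kg/m²) | w | Shift (kg/m²) | Share of 1.5 |
|---|---|---|---|---|---|
| 10% | 25% | 0.5 | 0.027 | 0.01 | 1% |
| 10% | 100% | 1 | 0.100 | 0.10 | 7% |
| 30% | 25% | 0.5 | 0.097 | 0.05 | 3% |
| 30% | 100% | 1 | 0.300 | 0.30 | 20% |
| 30% | 2/3 | 2 | 0.222 | 0.44 | 30% |

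The last row corresponds to 57 women replaced among 199.5 + 57 = 256.5 analysed. The sign of b is unknown, so each shift could go either way. The control mean does not move from this source. The table covers only error in the substituted values. The change in who is analysed, through adding attenders in one arm, comes on top and cannot be sized.

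**The case against.** The strongest reply is that little depends on this sentence. It permits and does not require, it carries a qualifier on appropriateness, and it is confined to secondary analyses. A reader might infer that the primary result is at risk. The article does not support that: the main analysis is the intention-to-treat comparison of 12-month BMI, and the intended method for missing primary data is multiple imputation.

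Second, the sentence speaks of missing weights in general, not of 12-month weights. The groups span the 36-week and 6-week visits, where a scale-measured session weight could be nearly contemporaneous and arguably better than self-report. The qualifier may mean exactly that, and matching windows could sit in an analysis plan that is not shown. This stands as far as it goes: carrying a 6-week weight to 12 months is allowed by the wording but not announced. No reading of the qualifier, however, gives control women a session weight or removes the selection of attenders. And the point is not a missing detail, because the article affirmatively permits the source.

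Third, nowhere does the article state in one sentence that control women have no session weights, or that none exist after 6 weeks. Both are inferences from what is and is not described.

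Fourth, a reader might call the use of session weights a breach of the rule in Protecting against bias. That is too strong. Session weighing is part of delivering the intervention, and the rule concerns collection of follow-up data. Reusing one as the other is a tension to clear up.

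**Conclusion.** The point holds in limited form. As the article describes its data, replacement by session weights can repair only the intervention arm, does so by engagement, and is at least about 20 or 46 weeks out of date at 6 or 12 months. The main intention-to-treat analysis is untouched; the exposure is in secondary and sensitivity analyses of weight.

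No size or direction can be established. The illustrative 0.01 to 0.4 kg/m² on the intervention mean depends on assumed replacement shares of 25% to 100% and assumed offsets of 0.5 to 2 kg/m². It is neither an estimate nor a bound, and its low end is negligible. It would be wrong to cite it as evidence that the trial's result will be biased by a given share of the 1.5 kg/m² target. The case for changing the text rests on the asymmetry between arms, and on the fact that a symmetric alternative is already planned.

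**What to change.** Amend the sentence in the missing-data paragraph as follows.

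- Do not use session weights to replace missing 6-month or 12-month weights.
- For missing 12-month BMI, use the multiple imputation already intended, respecting the clustering by unit, with researcher-measured BMI at baseline, 36 weeks gestation, 6 weeks and 6 months postpartum as predictors in both arms. These visits are already scheduled.
- Limit direct replacement to sources open to both arms, that is telephone self-report, in a separate sensitivity analysis.
- If session weights are used at all, confine them to a stated window around the 36-week and 6-week visits, in a labelled sensitivity analysis shown beside the result without them. Say how this fits with the separation of delivery and data collection in Protecting against bias.

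The cost is a few lines of text and no new data collection. The downside is that some intervention-arm values will be imputed rather than replaced by a measured weight.
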